### Data management and monitoring

All the data will be entered and stored in a password-protected computer. Hardcopy will be kept in a locker. No interim analyses will be carried out. To ensure high quality of the data, a double data entry method will be used. All documents and collected data will be kept for 7 years after the finish of study and then will be destroyed. The protocol and statistical results will be published in a scientific journal where the public will have access to all the results.

A data monitoring committee (DMC) will be formed and will include at least two faculty members from the participating universities, who are independent of the research team and who will not participate in any other aspect of the study. The data management process will be monitored by DMC regularly. All the data will be frozen and then locked to prevent further editing after the validation by the DMC. Only the DMC, the study research assistant and the principal investigator will have access to the final dataset.

### Statistical analysis

The proportion of patients with at least a four-point change in ADAS-cog and MMSE and the scores on C-DAD will be compared between the active treatment and placebo groups using the Chi-Squared test and independent sample t test, respectively. Missing data will be input using the last-observation-carried-forward (LOFC) approach. All patients randomized with at least one post-randomization measurement will be included in the primary analysis to follow the intention-to-treat principle. Analyses will be done with SPSS 19.0 package (SPSS, Chicago, IL).

To get a more comprehensive picture of the efficacy of DTD, a post-hoc analysis of the differences in the change of ADAS-cog and C-DAD sub-scores of the active treatment group will be compared between the active and placebo groups. To reduce the number of statistical comparisons, analyses will be performed with a hierarchical approach. To begin, the scores of ADAS-cog at week 24 (end of treatment) for the active treatment and placebo groups will be compared. If the difference is deemed statistically significant at a 2-sided *α*-level of 0.05, the scores of ADAS-cog at week 12 (half of treatment) and week 30 (end of observation period, that is, without treatment) will be compared between groups. C-DAD will be analyzed in the same manner as ADAS-cog.

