## Background

Alzheimer’s disease (AD) is an irreversible, progressive neurodegenerative disorder characterized by loss of cognitive functions, behavioral disturbances and daily living difficulties [1]. It is the most common type of dementia in the elderly [2]. Progressive atrophy is seen in all parts of the brain, especially in the hippocampus region, due to nerve cell death and tissue loss [3]. It is estimated that the number of people suffering from dementia over the world will rise from 24.3 million in 2005 to 81.1 million in 2040 [4]. It is expected that a new case of AD will be diagnosed every 33 seconds in America by 2050 [5].

AD has a devastating impact not only on sufferers, but also on caregivers, their communities and the health care system in general [6]. While much research is being done on many aspects of AD, including its basic biology, no drug has been found to alter the course of the disease [7]. Current pharmacological treatment for AD such as cholinesterase inhibitors (ChEIs) and memantine are symptomatic and may commonly associated with some side effects, such as nausea, vomiting, dizziness and anorexia [8]. Given that the efficacy is mild but with some side effects, patients often seek alternative treatments [9].

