## Methods/Design

### Study design

This study will be a double-blinded, randomized, placebo-controlled, add-on trial. Patients with mild to moderate AD will be randomly assigned to receive 24 weeks of either active herbal treatment or placebo (in a 1:1 ratio); they will be followed for a further 6 weeks’ observation period without treatment. This clinical study will be carried out at the Hong Kong Baptist University Chinese Medicine Specialty Centre. It has been approved by the Ethics Committee of the Hong Kong Baptist University’s Institutional Review Board (code: HASC/11-12/24) and registered with the Chinese Clinical Trial Registry (ChiCTR-TRC-12004548). If there is any amendment to the protocol, approval must be again sought from the Ethics Committee. Written informed consent will be obtained from every patient before participation in any study-related activity. The protocol design is based on the guidelines of Consolidated Standards of Reporting Trials (CONSORT) and Standard Protocol Items: Recommendations for Interventional Trials (SPIRIT) [see Additional file 1], and study results will be reported according to these guidelines as well.

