### Primary outcome and its assessment

A positive primary outcome of this study will be an increase of at least four points in the Alzheimer’s Disease Assessment Scale-cognitive subscale (ADAD-cog) [27] total score; this is considered to be a clinically meaningful increase [28]. Total scores of the ADAD-cog, Chinese version of Mini-Mental State Examination (C-MMSE) [29,30] and Chinese version of Disability assessment for dementia (C-DAD) score [31] will be used as secondary outcomes.

Outcome measurements will be carried out during the study visits at weeks 0, 12 (half of treatment), 24 (end of treatment) and 30 (end of observation period). Safety assessment, which includes reporting of adverse events (AEs), measurement of vital signs and physical examination, will be carried out throughout the study. In addition, laboratory safety screening of liver and renal function will be performed at week 24. Bilingual assessors, trained by the same neurology specialist [name] and clinical psychologist [name], will be blind to the treatment allocation.

Clinical assessment will be rescheduled within 7 days after the scheduled clinical visit in case of any unexpected condition such as severe weather conditions. Phone call reminders will be given to the caregivers one day before the days of assessment.

A home diary will be given to each study participant’s caregiver to record treatment and changes in the participant’s medical condition. Formal instruction for the home diary will be given during the first visit. Revision and checking of the diary will be carried out with the caregiver during each formal visit by the assessors. Compliance in taking the treatments will be determined by the record of the diary and the number of the returned medicine/placebo packages.

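### Last observation carried forward is fixed as the missing-data rule for a progressive disease scored only at weeks 0, 12, 24 and 30, which can bias the mean-score comparisons when dropout after week 12 differs by arm

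*Protocol article*

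**What the plan says.** The Statistical analysis section of the protocol article gives one missing-data rule, not limited to any endpoint or visit: "Missing data will be input using the last-observation-carried-forward (LOFC) approach". The analysis set follows: "All patients randomized with at least one post-randomization measurement will be included in the primary analysis to follow the intention-to-treat principle".

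The Background describes the disease as an "irreversible, progressive neurodegenerative disorder". The section on the primary outcome sets the schedule: "Outcome measurements will be carried out during the study visits at weeks 0, 12 (half of treatment), 24 (end of treatment) and 30". The Compliance strategy section adds visits at weeks 4, 8, 16 and 20, but these are not listed as outcome measurements.

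The mean scores are tested in steps: "To begin, the scores of ADAS-cog at week 24 (end of treatment) for the active treatment and placebo groups will be compared". Only if that comparison is significant are weeks 12 and 30 compared, and C-DAD is handled in the same way. Week 30 falls after treatment has ended; under Study design, "they will be followed for a further 6 weeks’ observation period without treatment".

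**The concern.** Carrying the last score forward assumes that a patient who leaves would not have changed afterwards. That sits badly with the protocol's own description of the disease. With so few assessments, the only post-baseline score that can fill week 24 is the one from week 12, so the second half of the treatment period is taken to bring no change.

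At week 30 the status of the patient also differs. The visit is there to see patients off treatment, but a missing score can be filled only from week 12 or week 24, both within the treatment period.

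Dropout need not be equal between arms. The Early termination section withdraws participants for severe side effects and for hypersensitivity to the study formula, and the second reason can truly arise only on active treatment. Any bias enters the week-24 mean difference, which opens the stepwise analysis. It also enters the effect estimate that the trial is meant to hand on to a full-scale study.

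**Working it through.** The documents give no dropout rate, rate of decline or standard deviation, so there is no figure of the plan's own to reproduce. The mechanism follows from the text. The sizes below rest on assumed inputs.

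**Who is affected**

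| Patient leaves | Last efficacy score | Consequence |
|---|---|---|
| Before week 12 | Baseline only | Excluded from the primary analysis (reading the required post-randomization measurement as an efficacy score) |
| Between weeks 12 and 24 | Week 12 | Week 12 fills weeks 24 and 30 |
| Between weeks 24 and 30 | Week 24 | Week 24 fills week 30 |

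**Assumed inputs**
- Decline D over 24 weeks is 2 to 4 ADAS-cog points and linear, so the decline from week 12 to week 24 is D/2 = 1 to 2 points.
- Dropout between weeks 12 and 24 is 30% or 40% in one arm and 10% in the other, unrelated to outcome.
- There are 20 patients per arm (Recruitment procedures) and no true effect.

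**Week-24 mean difference**

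Bias towards the arm losing more patients = (difference in dropout) × D/2.
- 30% vs 10%: 0.20 × 1 to 0.20 × 2 = 0.2 to 0.4 points.
- 40% vs 10%: 0.30 × 1 to 0.30 × 2 = 0.3 to 0.6 points.
- Equal dropout: 0 × D/2 = 0.
- If the split between arms is reversed, the sign reverses.

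For scale, with an assumed SD of 6 the standard error of the difference is 6 × √(2/20) = 1.9. The bias is then 0.2/1.9 = 0.1 to 0.6/1.9 = 0.3 standard errors.

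**Simulation** (40,000 trials; SD of change 5 at week 12 and 6 at week 24, correlation 0.7)
- 30% vs 10%: mean bias about 0.2 to 0.4 points, rejection rate 5.0% to 5.5%.
- 40% vs 10%: mean bias about 0.3 to 0.6 points, rejection rate 5.3% to 6.4%.
- Proportion improving by at least four points: the difference between arms moves by at most 0.8 percentage points.
- Pooled SD: falls by about 2% to 4%.

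**A true effect that grows linearly, with equal dropout d**

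A patient carried from week 12 shows half of the week-24 effect, so the share kept is (1 − d) + d × 0.5 = 1 − d/2. For d = 10% to 30% this is 95% to 85%. Here the rule dilutes the effect.

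**Week 30**

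Suppose a week-24 effect E has vanished by week 30 and a share m of each arm carries the week-24 score. The apparent remaining effect is m × E. For m = 10% to 30% it is 0.1E to 0.3E.

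**The case against.** The strongest reply is that the harm is small and that its inputs are assumed. Forty percent versus 10% means 8 versus 2 of 20 patients leaving within twelve weeks. Temporary interruption of the granules is allowed, and the plan adds a run-in, reminders, rescheduling and ongoing support. All patients take stable anti-dementia medication, and the Compliance strategy section expects patients on placebo to notice no difference, so decline may be slow. The primary outcome is a responder proportion, which hardly moves. The trial is a pilot that concedes its evidence will be weak.

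Most of this stands, and it limits the size of the point. It does not defend the rule. The bias is zero only if dropout is balanced and there is no effect, or if nothing changes after week 12, and the Background points against the latter. The responder result assumes that a responder is a patient who improves by four points. If the cut counted worsening, a separate simulation at 30% vs 10% (same SD at week 24, correlation 0.6) moved the difference by 2.0 to 3.3 percentage points for D = 2 to 4.

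Four stronger readings are tempting, and the documents do not support them.
- *The rule favours the active arm.* No dropout rate is given, and more withdrawal on placebo would reverse the sign.
- *Everyone who leaves early is frozen at a better score.* Those who leave before week 12 are excluded.
- *The week-30 comparison cannot show persistence.* Only missing scores are filled, so the contamination is in proportion to their share. That comparison also runs only after a significant week 24.
- *The full trial would be undersized through a shrunken SD, or the bias is a sizeable part of the four-point threshold.* The pooled SD falls by only 2% to 4% in the assumed cases. Four points is a within-patient cut and no yardstick for a group difference.

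The absence of sensitivity analyses from the article is not held against it, since these may be in a statistical analysis plan that is not shown.

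**Conclusion.** The point holds in a limited form. The article itself fixes a rule that assumes no change after the last visit, in a disease it calls progressive and with a schedule that leaves only week 12 to stand in for week 24. Under the assumed dropout and decline, the week-24 mean difference is biased by about 0.2 to 0.6 points towards the arm losing more patients, with type I error of about 5% to 6%. There is no bias with equal dropout and no effect, and there is dilution if an effect grows over time. The week-30 comparison is contaminated in proportion to its missing scores. The four-point-improvement proportion is hardly touched. What is at stake is mainly the mean-score comparisons and the effect estimate used to plan the next trial. The change should be made because it is cheap and the alternative is better, although the present rule would not by itself make the trial misleading.

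**What to change.** Replace the rule in the Statistical analysis section, before unblinding, as follows.
1. Analyse ADAS-cog and C-DAD with a likelihood-based repeated-measures model: baseline score, arm, visit and arm-by-visit interaction, unstructured covariance, and all observed scores at weeks 12, 24 and 30. Take the week-24 and week-30 contrasts from this model.
2. For the four-point outcome, multiply impute the total score within arm from the same variables and then apply the cut. Counting missing patients as non-responders can serve as a sensitivity analysis.
3. State that no score from the treatment period is carried to week 30.

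The cost is a change of wording and slightly more analysis work, which the named software can do. With about 20 patients per arm, the covariance and imputation models rest on few data, so the report should carry a small-sample caveat. The model relies on dropout being explained by the observed scores. That too is an assumption, though a weaker one than no change after leaving.

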### Compliance strategy

This will be a 30-week clinical trial, in which subjects will need to take study medication for 24 weeks with 8 regular visits (week 0, 4, 8, 12, 16, 20, 24 and 30). In order to maximize subjects’ compliance, first, we will have a thorough consent process for all participants; we will explain in detail the study schedule, potential side effects of treatment, and the responsibilities of the subjects. Second, we will screen potential subjects carefully during a 2-week run-in period in order to exclude ineligible patients or patients who are unlikely to comply with treatment regimen before randomization. Third, we will try to prevent dropouts by providing ongoing support to patients. A special e-mail account and a direct telephone line set up for this clinical trial will enable the study team to personally communicate with the patients. An information sheet will be given to each participant providing them and their caregivers with means of urgent contact. Extra visits and free medical care will be arranged for any participant who feels harmed by the trial protocol. Fourth, this is an add-on design [32], which means that the study treatment is added to their existing treatment. Certainly those participants receiving the placebo should not experience any difference in their condition, while those receiving the DTD should improve or at least remain the same.

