### Early termination

The trial will be terminated for a specific participant in the event of any of the following: (1) participant develops severe adverse side effect(s); (2) participant shows hypersensitivity towards DTD; (3) participant develops some other life-threatening condition or disease; or (4) participant chooses to participate in another Chinese medicine research project. In addition, any participant may voluntarily withdraw.

The whole research plan will be terminated under the following circumstances: (1) presence of serious adverse effect(s) related to Chinese herbal medicine with supportive evidence or (2) completion of all follow-up assessments.

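### The primary analysis set is called intention-to-treat but leaves out patients with no assessment after randomisation, and the first outcome assessment is at week 12

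*Protocol article*

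**What the plan says.** The analysis-set rule, in the Statistical analysis section, reads: "All patients randomized with at least one post-randomization measurement will be included in the primary analysis to follow the intention-to-treat principle". The same section gives one rule for gaps in the data: "Missing data will be input using the last-observation-carried-forward (LOFC) approach".

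The section on the primary outcome fixes the timing: "Outcome measurements will be carried out during the study visits at weeks 0, 12 (half of treatment), 24 (end of treatment) and 30", the last being the end of the observation period. The Compliance strategy section counts more visits than that, "8 regular visits (week 0, 4, 8, 12, 16, 20, 24 and 30", but no outcome measurement is assigned to weeks 4 or 8. What runs between outcome visits is safety: "Safety assessment, which includes reporting of adverse events (AEs), measurement of vital signs and physical examination, will be carried out throughout the study".

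The run-in comes before allocation. It is used to "exclude ineligible patients or patients who are unlikely to comply with treatment regimen before randomization". Losses after that point are therefore losses of randomised patients.

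Under Early termination, a patient's participation ends if, among other reasons, "participant develops severe adverse side effect(s); (2) participant shows hypersensitivity towards DTD". The section adds: "In addition, any participant may voluntarily withdraw".

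**The concern.** Intention-to-treat keeps every randomised patient in the arm to which chance assigned them. Here membership depends on something that happens after randomisation, namely being assessed at least once. The first opportunity comes halfway through the 24-week treatment period.

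If treatment influences who reaches week 12, and those who do not reach it differ in response from those who do, the two analysed groups are no longer the groups that randomisation formed. One termination reason, hypersensitivity to DTD, is tied to the active product by its wording, and severe side effects may also differ by arm. The last-observation rule gives no protection to a patient who is already outside the set.

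Two uses of the result are exposed: the test of the primary responder outcome, and the responder proportions themselves. The Abstract and Background say the trial should supply sample-size information for a full-scale trial.

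**Working it through.** **1. Reading the rule against the schedule.** Week 0 is taken as baseline. The outcome assessments after it are at weeks 12, 24 and 30. A patient with at least one of these is in the set; a patient with none is out. The excluded patients are thus those who leave before week 12 and are not assessed afterwards.

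**2. What one exclusion weighs.** Recruitment procedures plans at least 40 patients, 20 per group. One patient is 1/20 = 5% of an arm.

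**3. No plan figure to reproduce.** The Discussion says that a sample size calculation does not apply, and the article states no response rate, loss rate or power. Every rate below is an assumption.

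**4. Spurious difference when there is no true effect.** Let p be the true response proportion in both arms and L the fraction of an arm's non-responders lost before week 12, with no responders lost. The expected proportion among those analysed is p / [p + (1 − p)(1 − L)]. With p = 0.25:

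- L = 0: 25.0%
- L = 0.10: 0.25/0.925 = 27.0%
- L = 0.20: 0.25/0.85 = 29.4%
- L = 0.30: 0.25/0.775 = 32.3%

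In an arm of 20, L = 0.20 means 0.20 × 0.75 × 20 = 3 patients on average, and L = 0.30 means 4.5.

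The rejection rates come from exact enumeration of all outcomes with 20 per arm and an uncorrected chi-squared test at two-sided 0.05. The total is the sum of the two directions.

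| Non-responder loss, DTD / placebo | Spurious difference (points) | Rejections favouring DTD | Favouring placebo | Total |
|---|---|---|---|---|
| 0 / 0 | 0 | 2.6% | 2.6% | 5.1% |
| 20% / 0 | 4.4 | 5.2% | 1.2% | 6.4% |
| 30% / 0 | 7.3 | 7.4% | 0.8% | 8.2% |
| 20% / 10% | 2.4 | 3.8% | 1.7% | 5.5% |
| 20% / 20% | 0 | 2.6% | 2.6% | 5.2% |

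Totals are rounded after adding. A simulation of 200,000 trials gave totals of 5.2%, 6.4% and 8.1% for the first three rows, which agrees within simulation error. If the loss fell on the placebo arm instead, the same figures would hold with the sign reversed.

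**5. How few patients can matter.** Assume 8/20 DTD and 3/20 placebo responders, with early losses counted as non-responders. Chi-squared = 40 × (8×17 − 12×3)² / (20×20×11×29) = 3.13, p = 0.077. Now drop two DTD non-responders lost before week 12, giving 8/18 against 3/20. Chi-squared = 38 × (8×17 − 10×3)² / (18×20×11×27) = 3.99, p = 0.046. The difference grows from 25 to 29 points.

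**6. The proposed handling and the plan's own rule.** Carrying the week-0 score forward gives a change of 0, which is below the four-point threshold. Counting such a patient as a non-responder gives the same result.

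**The case against.** A reader might infer that everyone who stops the granules in the first 12 weeks is excluded. The text does not support that. Study medication allows temporary discontinuation for adverse events, and a patient who stops but is assessed at week 12, 24 or 30 stays in the set. Only those with no later assessment are lost.

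A reader might also infer that the plan will favour DTD by several points. That does not follow either. The 4.4 and 7.3 points need loss confined to DTD non-responders. With equal non-responder loss the spurious difference is nil. DTD loss of 20% unrelated to response also gives no expected difference. The rise in total two-sided error is more modest than the rise in the DTD-favouring direction.

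The term measurement is not defined. The article also uses it for vital signs, and there are visits at weeks 4 and 8. If a vital sign qualified a patient, week 0 could be carried forward and the exclusion would shrink. In a sentence about the primary efficacy analysis an outcome measurement is the natural meaning, but the looser one cannot be ruled out. The text needs correcting on either reading.

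Finally, sets of this kind are familiar in practice, this is a pilot, and the authors concede that positive evidence would still be weak. Renaming the set and reporting exclusions would cure the label. It would not cure the dependence of the primary comparison on post-randomisation events. Non-responder counting is itself a choice: if 20% of DTD patients left regardless of response, it would show 0.25 × 0.80 = 20% against 25%, because leaving counts as failure. This is why the present set is worth keeping as a sensitivity analysis.

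**Conclusion.** The point holds as a misstated and potentially biasing analysis set. It is a rule that the article states and labels wrongly, not detail left to a separate analysis plan. On the natural reading, patients who leave before week 12 and are never assessed again are removed from the responder comparison.

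Bias requires early loss that both differs by arm and is related to response. The documents make this possible but do not show that it will occur. Under the assumed scenarios it ranges from nil to about 7 percentage points, and its direction depends on which arm loses more non-responders. The conclusion about the label needs none of these assumptions; it needs only that measurement means outcome measurement and that week 0 is baseline.

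**What to change.** - Define the primary set as all randomised patients, analysed in their allocated arm.
- In the responder analysis, count patients with no post-baseline ADAS-cog as non-responders. How later missing values are handled, for patients who do have a post-baseline score, is a separate question that this change leaves alone.
- Keep the present set as a sensitivity analysis, call it modified intention-to-treat, and say that measurement means an outcome measurement.
- Report patients excluded before week 12 by arm, with reasons.

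Cost: the sentence is in the protocol, and the Study design section requires Ethics Committee approval for any amendment. At submission 36 subjects had been enrolled and the study was ongoing. There is a little more analysis, and the responder proportions may come out slightly lower than under the present set. No new visits, patients or data are needed.

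### The testing hierarchy is not tied to the responder primary and opens several separate entries at 0.05, so it thins out comparisons without giving familywise control of secondary claims.

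*Protocol article*

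**What the plan says.** Under Primary outcome and its assessment, the article names one primary outcome: "A positive primary outcome of this study will be an increase of at least four points in the Alzheimer’s Disease Assessment Scale-cognitive subscale". The total scores of ADAS-cog, C-MMSE and C-DAD are listed as secondary.

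The Statistical analysis section then does three things.

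- It compares the proportions with a four-point change on ADAS-cog and MMSE (chi-squared) and the C-DAD scores (t test), with no order or adjustment among them.
- It announces "a post-hoc analysis of the differences in the change of ADAS-cog and C-DAD sub-scores" between the arms.
- It sets a testing order, with the purpose given as "To reduce the number of statistical comparisons, analyses will be performed with a hierarchical approach". The first step is "To begin, the scores of ADAS-cog at week 24 (end of treatment) for the active treatment and placebo groups will be compared". The gate reads "If the difference is deemed statistically significant at a 2-sided" level of 0.05. Once it is passed, "the scores of ADAS-cog at week 12 (half of treatment) and week 30 (end of observation period, that is, without treatment) will be compared between" the arms. The paragraph ends: "C-DAD will be analyzed in the same manner as ADAS-cog".

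**The concern.** A testing order protects its claims only if it starts from the result that carries the trial's conclusion and each later step depends on the earlier ones. Here the responder primary is not a step. The ladder begins on a secondary score and continues if the primary fails. C-DAD does not wait for ADAS-cog, and alpha is not split between the two scales. After a significant week 24, weeks 12 and 30 are both tested at 0.05 with no order between them. The MMSE proportion belongs to no step, and no step names the sub-scores.

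At stake is how secondary results will be read. The abstract says that success will justify a large-scale trial, and the Discussion hopes to learn which symptoms the treatment improves. With 20 patients per arm, a chance finding on a secondary score could be reported as significant beside a failed primary, and could steer the choice of endpoint for the next trial.

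**Working it through.** The article states no familywise error rate, power or calculated sample size, so there is no overall figure to reproduce. Its only error rate is the two-sided 0.05 of each gate. In simulation under the null with 20 per arm, each week-24 t test taken alone rejected in about 5% of trials, so that level holds per test.

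**Inputs from the article:** 20 per arm, 1:1 (Recruitment procedures); two-sided 0.05, chi-squared and t tests (Statistical analysis).

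**Assumed, because the article does not give them:** responder rate 30%-50%; correlation between scales 0-0.7; correlation between visits 0.5-0.8; responder status judged at week 24. The responder and the ADAS-cog score come from the same simulated change. The chi-squared test has no continuity correction.

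**Entry tests that no earlier result gates:** (1) ADAS-cog responder, (2) MMSE responder, (3) ADAS-cog score at week 24, (4) C-DAD score at week 24. C-DAD is counted once, although it appears both in the opening comparison and in its own ladder.

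**Step 1: the two week-24 gates, ADAS-cog and C-DAD.**
- Independent: 1 - 0.95² = 0.0975. Upper bound: 2 × 0.05 = 0.10.
- Simulated, correlation 0.7 down to 0: about 0.08 to 0.10.

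**Step 2: all four entry tests.**
- Independent: 1 - 0.95⁴ = 0.1855. Upper bound: 4 × 0.05 = 0.20.
- Independence cannot hold, because test (1) dichotomises the variable used in test (3). Simulated with that link: about 0.13 (responder rate 50%, correlation 0.7) to 0.17 (responder rate 30%, correlation 0).

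**Step 3: a ladder opens while the primary is not significant.** Simulated under the null: about 0.06 to 0.08.

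**Step 4: weeks 12 and 30 within one ladder.** Suppose there is a true difference at week 24 and none at the other two visits. The two tests then give at least one false positive with probability 1 - 0.95² = 0.0975 if independent, and about 0.078 to 0.093 in simulation with visit correlation 0.8 to 0.5.

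**Step 5: what gating everything on the primary would cost.** Power of the chi-squared test with 20 per arm, at assumed responder rates of 30% vs 50%:
- standard error under the null: √(2 × 0.4 × 0.6 / 20) = 0.155
- standard error under the alternative: √((0.3 × 0.7 + 0.5 × 0.5) / 20) = 0.152
- Φ((0.20 - 1.96 × 0.155) / 0.152) ≈ 0.25

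At 20% vs 40% the same formula gives about 0.28, and exact binomial enumeration gives 0.29.

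**The case against.** The strongest reply is that the plan never promised error control. Its stated aim is fewer comparisons, and the gate delivers that: if week 24 fails, weeks 12 and 30 are not tested. This stands. A reader might infer that the procedure misses its own target for false positives, but the article sets no such target.

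Second, there is one named primary, and the ladder does not alter its error rate. This also stands. A reader might infer two rival primary results, but the Primary outcome section defines a positive primary outcome by the responder criterion alone.

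Third, the sub-scores may be gated after all. The hierarchy sentence directly follows the sub-score sentence and may be meant to govern it. It is tempting to say that the sub-scores are tested freely and to attach a very large error rate, but the text supports either reading and gives no number of sub-scores. What can be said is that their place is unclear.

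Fourth, this is a pilot whose Discussion concedes that even a positive result would be weak evidence. That lowers the stakes. It does not remove them, because the same article says that success would justify a large trial.

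**Conclusion.** The concern holds in limited form. The hierarchy is detached from the primary endpoint, gives each scale its own entry at 0.05 and leaves the sub-scores unplaced. It therefore gives no familywise protection to secondary claims. Under the null, the chance of at least one false positive is about 8%-10% for the two week-24 gates and about 13%-17% for the four entry tests, and a ladder opens beside a non-significant primary in about 6%-8% of trials. These figures rest on 20 per arm and on the assumed responder rates and correlations. The independence value of 18.55% for four tests is too high, because the responder and the score share the same data. The primary comparison keeps its own error rate. This is a low-cost improvement to the reporting of secondary results and does not undermine the primary test.

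**What to change.** In the Statistical analysis section:

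- State that the between-arm comparison of the ADAS-cog four-point responder proportion is the only test supporting a formal efficacy claim. Name its visit, since the article gives none for the responder.
- Report the ADAS-cog, C-MMSE and C-DAD scores, the MMSE proportion, the week-12 and week-30 comparisons and all sub-scores as between-arm estimates with 95% confidence intervals and no significance claims.
- Replace the post-hoc label with prespecified exploratory.

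The cost is a few sentences and the loss of formal claims on secondary outcomes, which is small in a pilot that already calls its evidence weak.

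A single fixed sequence starting at the responder test, each step at 0.05 and stopping at the first failure, is an optional alternative and would hold familywise error at or below 0.05. With power of about 25%-29% at the assumed rates, it would usually stop at the first step, so the exploratory labelling suits this trial better.
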